## Abstract

**Background:**

Community-based programs aimed at improving cooking skills, cooking confidence and individual eating behaviours have grown in number over the past two decades. Whilst some evidence exists to support their effectiveness, only small behavioural changes have been reported and limitations in study design may have impacted on results.

This paper describes the first evaluation of the Jamie Oliver Ministry of Food Program (JMoF) Australia, in Ipswich, Queensland. JMoF Australia is a community-based cooking skills program open to the general public consisting of 1.5 hour classes weekly over a 10 week period, based on the program of the same name originating in the United Kingdom.

**Methods/Design:**

A mixed methods study design is proposed. Given the programmatic implementation of JMoF in Ipswich, the quantitative study is a non-randomised, pre-post design comparing participants undergoing the program with a wait-list control group. There will be two primary outcome measures: (i) change in cooking confidence (self-efficacy) and (ii) change in self-reported mean vegetable intake (serves per day). Secondary outcome measures will include change in individual cooking and eating behaviours and psycho-social measures such as social connectedness and self-esteem. Repeated measures will be collected at baseline, program completion (10 weeks) and 6 months follow up from program completion. A sample of 250 participants per group will be recruited for the evaluation to detect a mean change of 0.5 serves a day of vegetables at 80% power (0.5% significance level). Data analysis will assess the magnitude of change of these variables both within and between groups and use sub group analysis to explore the relationships between socio-demographic characteristics and outcomes.

The qualitative study will be a longitudinal design consisting of semi-structured interviews with approximately 10-15 participants conducted at successive time points. An inductive thematic analysis will be conducted to explore social, attitudinal and behavioural changes experienced by program participants.

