### Piloting

The questionnaire was piloted in a 3 step process to test the design, content and potential delivery methods. Following comment by the reference group and academic colleagues on content and layout/design, a paper-based version of the questionnaire was piloted with a sample (N = 30) of the current JMoF population. Feedback was invited through informal focus group sessions, facilitating the identification of any questions that were ambiguous, sensitive or required further development.

The final stage of piloting involved testing the questionnaire in an online format whilst simultaneously testing the online survey distribution system and the likely response rate. As the survey distribution required integration between the JMoF participant database and the survey platform, Qualtrics™ [27], the piloting tested that these two components were effectively integrated and capable of providing the necessary information needs.

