### Sample size

Given that the specific questions developed for this study to measure confidence to cook (cooking self-efficacy) have not been previously employed, a precise sample size calculation for this primary outcome could not be calculated given the absence of a priori baseline measures, measures of effect size and measures of variance (standard deviation).

Sample size calculations around the second primary outcome of a change in vegetable intake between the two groups assumed the use of a split-plot anova and F test for interaction given the wait list design. The literature does not provide clear guidance with regards to an expected effect size for a program of this nature [29,30]. However, as there is some evidence from Wrieden et al that an effect size of one serve per day may be too large for a program of this nature [20], sample size calculations are based on an effect size range likely to be achieved [29,30]. For an effect size of 0.5 serves a day, starting from a mean daily consumption at baseline of 2.5 serves per day [13,23], 250 subjects per group will be required at 80% power (0.05 significance). In the event that accrual is slower than expected, recruiting at least 140 participants will give 80% power for an effect size of 0.7 serves a day. There will be no analysis of the data before accrual has closed.

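### The 250 per group needed for 80% power is also the recruitment target, so the stated power holds only if every recruit returns the 10-week survey

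*Protocol article*

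**What the plan says.** The Sample size section of the protocol article bases the vegetable-intake calculation on a group-by-time test; it "assumed the use of a split-plot anova and F test for interaction given the wait list design". The inputs given are the effect ("For an effect size of 0.5 serves a day"), a baseline level ("starting from a mean daily consumption at baseline of 2.5 serves per day"), and the result: "250 subjects per group will be required at 80% power (0.05 significance"). No SD, within-person correlation or loss rate is stated.

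The Abstract (Methods/Design) turns the same number into the enrolment target: "A sample of 250 participants per group will be recruited for the evaluation", for the same 0.5 serves and the same 80% power.

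The fallback in the Sample size section works the same way. It says that recruiting 140 or more gives 80% power for 0.7 serves.

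Elsewhere, Study design gives controls two surveys, 10 weeks apart. Data collection plans a postal version for people who do not respond online. The Discussion lists follow-up of non-responders and incentives among the measures against selection bias. The only questionnaire incentive described under Recruitment goes to intervention participants who complete the six-month survey.

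**The concern.** A sample-size formula for a change comparison returns the number of people who contribute a change. Here that number and the number to be recruited are identical. Someone who completes T1 but not T2 counts towards recruitment but adds nothing to the between-group test of change. Unless 250 already contains an allowance that the article does not mention, every lost 10-week survey takes the power below the stated 80%.

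This is more than a detail left out of a condensed article. The article says that recruiting these numbers provides the power, and it says so at both sample sizes. A reader would take a non-significant vegetable-intake result as coming from a comparison with 80% power for 0.5 serves, when the number of complete pairs may not support that. The one described survey incentive comes after the 10-week comparison and is not offered to controls, so it does little to protect the data this test needs.

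**Working it through.** **Inputs**
- Number required per group: 250 (Sample size). Number recruited per group: 250 (Abstract).
- Effect δ = 0.5 serves/day; power 80% (Sample size).
- Significance level: 0.05 (Sample size: "at 80% power (0.05 significance"). Two-sided is my assumption. The Abstract has "at 80% power (0.5% significance level"), which conflicts; see the last step.
- SD of change σ: not stated. Loss between T1 and T2, d: not stated. Both are assumed below.

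**Step 1: the test.** With two groups and two time points, the split-plot interaction test is equivalent to a two-sample comparison of change scores, so

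n per group = 2σ²(z₁₋α/₂ + z_power)² / δ², with z₁₋α/₂ + z_power = 1.9600 + 0.8416 = 2.8016.

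**Step 2: the plan's own figure.** Without an SD, 250 cannot be reproduced. Solving backwards, on the premise that 250 contains no allowance:

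σ = 0.5 / (2.8016 × √(2/250)) = 0.5 / 0.2506 = 1.995.

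A rounded SD of 2.0 gives n = 252, so 250 is a plausible no-allowance result. At σ = 1.995, 250 complete pairs give exactly 80.0%, with nothing in reserve.

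**Step 3: power after loss.** With 250(1 − d) pairs per group,

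power = Φ(δ / (σ√(2/n)) − 1.96) = Φ(2.8016 × √(1 − d) − 1.96).

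The back-solved SD cancels. The result depends on the no-allowance premise, the significance level and d. The detectable effect at 80% power is likewise 0.5/√(1 − d).

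| Assumed loss | Pairs per group | Power for 0.5 serves | Effect detectable at 80% |
|---|---|---|---|
| 0% | 250 | 80.0% | 0.50 |
| 4% | 240 | 78.4% | 0.51 |
| 5% | 238 | 78.0% | 0.51 |
| 10% | 225 | 75.7% | 0.53 |
| 20% | 200 | 70.7% | 0.56 |
| 30% | 175 | 65.0% | 0.60 |

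For 20% loss: 2.8016 × √0.8 = 2.5058; 2.5058 − 1.96 = 0.5458; Φ = 0.707.

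**Step 4: the fallback.** Scaling 250 per group from 0.5 to 0.7 serves gives 250 × (0.5/0.7)² = 127.6, so 128 per group. The 140 is therefore far more plausibly per group than a total. The two figures do not share one SD. At σ = 1.995, 140 per group gives 83.5% power, a small margin. If 140 is instead taken as exact, σ = 0.7 / (2.8016 × √(2/140)) = 2.09, and 250 per group then gives 76.3% before any loss. The fallback does not show slack in the 250.

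**Step 5: significance level.** Had the calculation used the Abstract's 0.5% (two-sided), z₁₋α/₂ + z_power = 2.8070 + 0.8416 = 3.6487. Power at that level after 20% loss would be Φ(3.6487 × √0.8 − 2.8070) = Φ(0.456) = 67.6%. The direction is the same.

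**The case against.** The strongest objection is that the size of the shortfall cannot be found from the article. The SD is back-solved on the premise that 250 holds no allowance, so it cannot also prove that premise. The Sample size section says only subjects, which could mean analysable people. If the true SD of change were smaller, there would be slack: at SD 1.53 (what 250 would imply under the Abstract's 0.5% level), a test at 0.05 has about 95% power with 250 pairs per group and still about 81% with 150. This stands as far as the figures go, and the table is an illustration only. It does not remove the point, because the article ties the stated power to numbers recruited, both in the Abstract and in the fallback. That wording speaks against a hidden allowance, although it cannot strictly exclude one.

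Reading 140 as a total (70 per group) would also imply a small SD, about 1.48, and ample power. The scaling to 128 per group makes that reading implausible.

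Three stronger readings are tempting and are not supported:
- A reader might infer that the pilot supplied a loss rate that was then ignored. Piloting describes "simultaneously testing the online survey distribution system and the likely response rate", which is response to an invitation. No T1-to-T2 follow-up in the pilot is described, so that rate would be the wrong input.
- A reader might call loss certain. The article expects non-response and plans to chase it, but gives no rate, and loss under about 5% would hardly matter.
- A reader might expect a mixed model to recover the power. With two time points, people with baseline only carry almost no information on change.

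**Conclusion.** The point stands as a mismatch between a stated property and the stated recruitment. The article requires 250 per group for 80% power and recruits exactly 250 per group, so the 80% holds only with complete 10-week return, which the article itself does not expect. No arithmetic in the article is shown to be wrong, and the shortfall cannot be fixed from its contents.

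If 250 contains no allowance and the test is two-sided at 0.05, power is about 76%, 71% and 65% at 10%, 20% and 30% loss. The loss rates are assumptions. A reader might take these percentages as the trial's actual power. They are not, because the article gives neither the SD of change nor the loss. The point is worth correcting because the power statement governs how a non-significant vegetable-intake result is read, and the correction is cheap.

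**What to change.** In Sample size, and in the matching Abstract sentence:
1. State that 250 per group, and 140 per group in the fallback, is the number with vegetable-intake data at both T1 and T2.
2. State the assumed SD of change and the assumed T1-to-T2 loss, with the basis for each. If 250 already includes an allowance, say so and give the number of pairs behind it.
3. If recruitment stays at 250, restate the power, or the effect detectable at 80% power, for the expected number of complete pairs. On the illustrative premise above, that is about 0.56 serves at 20% loss or 0.60 at 30%.

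The cost is one or two revised sentences. A larger target is optional: keeping 250 pairs would need 250/(1 − d) recruits per group, which is 278 at 10% loss, 313 at 20% and 358 at 30%. The correction does not depend on it.

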**Discussion:**

This evaluation will contribute to the evidence of whether cooking programs work in terms of improving health and wellbeing and the underlying mechanisms which may lead to positive behaviour change.

**Trial registration:**

Australian and New Zealand Trial registration number: ACTRN12611001209987.

## Background

Cooking skills programs have been described as a practical illustration of how to simultaneously change knowledge, attitudes and behaviours around healthy eating practices [1]. Interest in cooking has been stimulated by media attention afforded to celebrity chefs and popular prime time television cooking programs. However, the need to promote cooking skills to individuals has in part stemmed from a decline in the traditional pathways by which individuals learn to cook [2], and from the hypothesis that a decline in cooking skills may have contributed to the growth in nutrition-related disease in certain sub-sections of western populations [3]. In Australia, Winkler investigated the relationship between a lack of confidence to cook and the purchasing of fruit and vegetables. The author concluded that cooking skills may contribute to socio economic differences in dietary intake and that promotion of such could be a useful strategy to improve fruit and vegetable intake [4].

In the past two decades, there has been an increase in the number of not-for-profit community-based cooking skills programs both in Australia and internationally [5-8]. Such programs have been conducted in a variety of community and institutional settings, targeting different sub-populations and varying in purpose; however, they are predominantly aimed at increasing confidence to cook, promoting healthy eating, addressing health inequalities and increasing access to healthy food [9].

Whilst there is emerging evidence of the effectiveness of these adult programs in terms of increasing confidence to cook and creating positive dietary change, this evidence, to date, has been based on small scale evaluations that are subject to methodological limitations [9]. In a recent systematic review of the effectiveness of adult community cooking programs conducted in the United Kingdom, only one evaluation was identified as suitably robust to provide reliable findings with respect to program effectiveness [10]. This highlights the need for more rigorous, larger scale studies to examine the range of impacts and outcomes of cooking skills programs and the underlying potential mechanisms for change in individual behaviour. At the same time, study designs must take account of the challenges associated with evaluation in community settings and be practical, feasible and sensitive to all stakeholders involved.

### The Jamie Oliver Ministry of Food program, Australia

This methods paper describes the evaluation framework and design for the Jamie Oliver Ministry of Food program (JMoF) Australia, Ipswich site. The JMoF program was originally developed by Jamie Oliver, a renowned celebrity chef and food author based in the United Kingdom (UK). JMoF Australia has been specifically adapted for the Australian setting. It is a community focused program that teaches basic cooking skills and good nutrition to non-cooks. It consists of 10, weekly, 1.5 hour cooking skills classes aimed at getting people of all ages and backgrounds cooking simple, fresh, healthy food quickly and easily [11]. Participants pay AUD10 per class and, where this may pose a barrier to entry, subsidies are made available.

JMoF was pioneered as a community-based cooking skills program in Rotherham, UK in 2008 and since then, other centres have opened in Bradford and Leeds and a mobile centre in the North West of the UK. These centres were reliant on funding mostly from local councils and to a lesser extent, charities and the private sector. The first Australian site opened in Ipswich in the state of Queensland in April 2011 co-funded by a local philanthropic non-government organisation (NGO), The Good Foundation (TGF), and the Queensland Department of Health. Ipswich was intentionally chosen given its significant low socio-economic status population [12] and increasing levels of overweight and obesity [13].

### Objectives of the JMoF program Australia

Consultation occurred between TGF, Queensland Health (as program co-founder) and the program evaluation team to describe program objectives of the JMoF program Australia in sufficient detail to be tested in an applied evaluation. The following program objectives resulted:

1. To provide opportunities, to people of different age and demographic background, to experience and learn how to cook healthy meals quickly and cheaply.

2. To increase program participants’ cooking skills, knowledge and self-efficacy.

3. To increase program participants’ enjoyment of food and social connectedness.

### Theoretical perspectives

A program logic model was developed as a framework to describe the potential pathways to behaviour change, and in turn to guide evaluative enquiry (Figure 1). Whilst some steps along the logic pathway were grounded by emerging or convincing evidence, other areas were backed by limited evidence, thereby requiring further hypothesis testing.

**Figure 1 F1:**
[figure not shown]
JMOF Australia program logic model.

Theoretical frameworks were not explicitly stated for the JMoF Program. However, Carahar and Lang, 1999 [2] have identified theoretical perspectives specific to cooking skills that are in keeping with the objectives of the JMoF program and its evaluation - cooking skills empower individuals in preparation for healthy eating, encourage self-esteem and provide opportunities for leisure and enjoyment.

Other theories that resonate with the program include Kolb’s concept of experiential learning [14] which identifies the importance of empowering participants with practical “get your hands dirty” experience in learning to cook from scratch as a basis for skill acquisition, and Bandura’s Social Cognitive Theory [15] which states that changes in attitudes and beliefs and the development of self- efficacy (i.e. confidence in cooking) are central to influencing behaviour change. Bandura’s Social Learning Theory [16] also states that modelling is an important component of the learning process and that opportunities for practising learned behaviours and positive reinforcement are needed for learning to take place. An important element in the learning process is role model credibility [17].

## Methods/Design

The evaluation will be conducted over a 2.5 year period from late 2011 to early 2014. The evaluation was approved by the Deakin University Human Research Ethics Committee (HEAG-H 117_11) in October 2011. Evaluation project governance will be provided by a reference group (comprising personnel from the TGF team and the research team members) which will meet twice yearly to oversee the project. A representative from Queensland Health will be invited to attend Reference Group meetings, when appropriate.

The evaluation will use a questions-oriented approach [18] derived primarily from the JMoF Program objectives. It will also incorporate additional economic questions of relevance to potential government funders and program stakeholders. A longitudinal mixed methods evaluation design will be employed. The quantitative and qualitative components will be conducted sequentially, with baseline quantitative data informing sampling for the initial qualitative interviews. Each component will then be analysed independently, with merging of data occurring at the interpretation stage [19].

### Quantitative study

### Research questions

The quantitative component of the evaluation will answer the following research questions:

1. Does the JMoF program increase participants’ skills, knowledge, attitudes, enjoyment and satisfaction of cooking and cooking confidence (self-efficacy)?

2. Does the JMoF program result in broader positive outcomes for participants in terms of behaviour change to a healthier diet, more affordable healthy meals, improved self-esteem and social connectedness?

### Outcome measures

There will be two primary outcome measures: a change in cooking confidence (self-efficacy) and a change in self-reported mean vegetable intake (serves per day). Secondary outcome measures will include change in self-reported measures of: (i) mean daily fruit intake, (ii) mean weekly takeaway/fast food intake, (iii) frequency of cooking the main meal from basic ingredients, (iv) nutrition knowledge, (v) attitudes towards cooking, (vi) willingness to try new foods and (vii) enjoyment and satisfaction of cooking. Change in psycho-social measures such as (viii) global self-esteem and (ix) social connectedness in relation to cooking and eating will be measured as will (x) a change in participant’s total expenditure on food.

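### Two primary outcomes are named with no success rule or alpha allocation, while the sample size gives the full 0.05 to vegetable intake alone

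*Protocol article*

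**What the plan says.** The Abstract and the Outcome measures section agree on the primaries. The latter reads "There will be two primary outcome measures" and lists cooking confidence and daily vegetable intake, both as changes. Neither outcome is placed above the other.

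The Sample size section treats them differently. For cooking confidence it reports that "a precise sample size calculation for this primary outcome could not be calculated given the absence of a priori baseline measures", and it gives no significance level. For vegetable intake the calculation "assumed the use of a split-plot anova and F test for interaction given the wait list design", and the result is "250 subjects per group will be required at 80% power (0.05 significance". The effect behind that number is stated as "For an effect size of 0.5 serves a day, starting from a mean daily consumption at baseline of 2.5 serves per day".

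The Abstract describes the same vegetable calculation with another level: "to detect a mean change of 0.5 serves a day of vegetables at 80% power (0.5% significance level".

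The quantitative Data analysis section lists two-sample and paired t tests resting on a split-plot Anova, chi-squared tests and regression. It states no alpha, no success criterion and no link between the two primaries. The quantitative Research questions put cooking confidence under the first question and healthier diet under the second.

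**The concern.** With two primaries of equal standing and the full 0.05 already assigned to one of them, the natural working assumption is that the other is tested at 0.05 as well. If a positive result on either were then reported as success on a primary outcome, the 0.05 in the sample size calculation would not be the error rate of that claim. Both outcomes are self-reported, in a non-randomised comparison where participants know their group, so a chance result on one of them should not carry the conclusion unaided.

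The sizing is also affected. The stated 250 per group matches its stated power only if vegetable intake keeps the whole 0.05. A later even split of alpha would make the published power figure wrong.

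**Working it through.** **Inputs.** From the Sample size section: 250 per group, difference 0.5 serves a day, power 80%, level 0.05. From the Abstract: 0.5% for the same calculation. Not stated: the SD, the sidedness (two-sided assumed), the level for cooking confidence, the correlation between the outcomes.

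**1. The plan's own figure.** The 250 cannot be reproduced without an SD, so solve n = 2·SD²·(z₁₋α/₂ + z₀.₈)²/δ² for SD:

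- α = 0.05: SD = 0.5·√125/(1.960 + 0.842) = 5.590/2.802 = 1.995, about 2.0 (a standardised effect of 0.5/1.995 = 0.251).
- α = 0.005: SD = 5.590/(2.807 + 0.842) = 1.53.

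Either level fits 250 with some SD, so the sample size does not show which is meant. If the SD is 2.0, the level 0.005 would need about 425 per group, and 250 would give about 50% power.

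**2. Familywise error if each is tested at 0.05 and either suffices.** For independent tests, 1 − 0.95² = 0.0975. For correlated two-sided tests (bivariate normal):

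| Correlation of test statistics | Familywise error |
|---|---|
| 0 | 9.75% |
| 0.3 | 9.5% |
| 0.5 | 9.1% |
| 0.7 | 8.3% |
| 0.9 | 7.0% |

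**3. The same quantity under other readings (independent tests).**

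- 0.005 for vegetables and 0.05 for confidence: 1 − 0.995 × 0.95 = 5.5%.
- 0.005 for both: 1 − 0.995² = 1.0%.
- Both primaries required, each at 0.05: not above 5%.

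**4. Vegetable power under an even split, SD 1.995.** The expected test statistic is 0.5/(1.995·√(2/250)) = 2.802. At level 0.025 the critical value is 2.241, so power = Φ(2.802 − 2.241) = 71%. Restoring 80% needs 2·1.995²·(2.241 + 0.842)²/0.25 = 303 per group.

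**5. Vegetable power under Holm.** For independent tests, vegetables succeed with probability 0.712 + (0.800 − 0.712)·π, where π is the power for confidence at 0.025.

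- No confidence effect (π = 0.025): 0.712 + 0.088 × 0.025 = 71%.
- Effect of 0.25 SD (π = Φ(0.25·√125 − 2.241) = 0.71): 0.712 + 0.088 × 0.71 = 77%.
- Effect of 0.5 SD (π about 1): 80%.

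**6. Vegetable power under a fixed sequence, confidence first.** Vegetables keep 0.05 but are tested only if confidence succeeds. With a confidence effect of 0.25 SD, power for confidence at 0.05 is Φ(2.795 − 1.960) = 0.80, so under independence vegetables succeed with probability 0.80 × 0.80 = 64%. With no confidence effect that probability cannot exceed 5%. With a large confidence effect it is close to 80%.

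**The case against.** The strongest reply is that the article never says what the 9.75% needs. A reader might infer that the plan tests each primary at 0.05 and calls the program effective if either succeeds, and so that 9.75% is the trial's error rate. The text does not support that:

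- The level 0.05 appears once, for vegetable intake, and the Abstract gives 0.5% for the same calculation.
- Cooking confidence has no level at all.
- The primaries sit under separate research questions, so each could be reported as answering its own question. Whether familywise control is then needed is a matter of judgement.
- Both outcomes come from the same people and the same questionnaire, so positive correlation is plausible and 9.75% is the upper end of the table.
- The article nowhere claims an overall 5% error rate.

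All of this stands, and it makes the figure conditional.

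It can also be said that a multiplicity rule normally belongs in the SAP, which is not shown. As an answer to a missing procedure, that is fair. It does not cover what the article has already fixed: two equal primaries, and a sample size that spends the whole 0.05 on one of them. An unseen rule that splits alpha would contradict the published power. A rule that leaves vegetables the full 0.05 would have to be a joint requirement or an ordering, and the article indicates neither.

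**Conclusion.** The point holds in conditional form. The article fixes two co-equal primaries and sizes one of them at the full 0.05, without saying what counts as success or how alpha is shared. If each is tested at 0.05 and either suffices, the familywise error is up to about 9.75%, falling to 9.1% at correlation 0.5 and 7.0% at 0.9. If both are required, it does not exceed 5%. The article does not say which applies, so no single error rate can be attributed to the trial.

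The power figures rest on a two-sided test and an SD of change of about 2.0. That SD is implied by 250 per group at 0.05 and is not stated. The Holm range of 71% to 80% further depends on a confidence effect that the article says it cannot specify. The conflict between 0.05 and 0.5% is in the text itself and comes first, because it changes every figure here.

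**What to change.** 1. Reconcile the level in the Sample size section (0.05) with the level in the Abstract (0.5%).
2. Name the primary comparison for each outcome as the between-group difference in T1-T2 change. This matches the interaction test assumed in the sizing and the two time points at which controls are surveyed.
3. State one rule that holds the two primary comparisons at 5% overall:
   - **Holm:** the smaller p-value against 0.025 and, if that succeeds, the other against 0.05. Add that vegetable power at 250 per group lies between about 71% and 80% depending on the confidence result, assuming an SD of change of about 2.0.
   - **Fixed sequence:** confidence at 0.05, then vegetable intake at 0.05 only if confidence succeeds. This keeps the alpha used for sizing, but no vegetable claim is possible if confidence fails.

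The cost is a sentence or two in the Data analysis section and a qualified power statement. Recruitment and data collection do not change. Under Holm the price is at most about 9 points of vegetable power. The article rules out any analysis before accrual closes, so the rule should be set and recorded before then.
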